### Recruitment strategy

The study will consist of at least 30 of the 68 available preschools (from Early Childhood Services Management (ECMS), Victoria) and aims to retain a total of at least 300, 4–5 year old children, who attend preschool together with their English speaking parents (because the program is only offered in English); the children will be in their final year of preschool. With a likely quota of 10 participants per preschool, 30 preschools (15 matched pairs) are required, 15 randomized to each arm of the study. Our formative work indicated a potential 11% attrition rate. Making a prudent allowance for attrition of up to 20%, 360 4–5 year old children and their parents will therefore be recruited and the adjusted number of preschools per study arm is likely to be 18 (i.e. a total of 36 kindergartens in 18 pairs).

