### Power, sample size and retention

The primary outcomes for this intervention are children’s knowledge about healthy eating, active play and the sustainability consequences of their food and toy selections. However, we decided to power our sample for the secondary outcome of child eating because we wanted to evaluate the extended effect of delivering the curriculum interventions to preschool children and we could base our sample size calculations on Australian data that provide relevant parameter estimates from three studies in the Barwon-South Western region of Victoria (*n* = 950) with children aged 2–4 years of age [31]. Vegetable consumption will require the largest sample size to demonstrate change over time, compared to other dietary outcomes, such as sweetened drinks, packaged snacks (e.g., chips, muesli bars), confectionary/chocolate, cake/sweet biscuits, and fruit, based on sample size analyses. As there are no quantitative dietary recommendations for children less than 4 years old in Australia, we adopted a suggestion of a 25% increase in vegetable consumption as a minimum target [32]. Based on findings that 63% of pre-school children had ≤1 serve of vegetables per day, we assume that the intervention will have a 25% absolute effect, that is the proportion of children in the intervention group who only have ≤1 serve of vegetables per day will change from 63% to 43%. We calculated the sample size necessary to detect a clinically meaningful difference in vegetable consumption, significant at the 0.05 level, with a power of 0.8; this calculation resulted in a sample of 150 children in each group. Making a prudent allowance for attrition of 20% (based on our previous research with preschool children and their parents), the adjusted number per treatment condition is 180. A total of 360 4-year-old children will therefore be recruited. This sample size is also sufficient to detect medium effect sizes in both the primary and secondary measures with a power of .8 at α = 0.05 [33].

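### The 20% attrition allowance is added as 150 × 1.2 = 180 per arm, so a 20% loss leaves 144 per arm (288 in total), slightly below the plan's own 150 and 300

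*Protocol article*

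**What the plan says.** Two sections of the Protocol article set the recruitment target.

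- **Power, sample size and retention.** On the requirement: "this calculation resulted in a sample of 150 children in each group". On losses: "Making a prudent allowance for attrition of 20% (based on our previous research with preschool children and their parents". The result: "the adjusted number per treatment condition is 180. A total of 360 4-year-old children will therefore be recruited".
- **Recruitment strategy.** The study "aims to retain a total of at least 300, 4–5 year old children". Before any allowance, "With a likely quota of 10 participants per preschool, 30 preschools (15 matched pairs) are required, 15 randomized to each arm of the study". The section then reports that "Our formative work indicated a potential 11% attrition rate" and continues: "Making a prudent allowance for attrition of up to 20%, 360 4–5 year old children and their parents will therefore be recruited". On clusters, "the adjusted number of preschools per study arm is likely to be 18 (i.e. a total of 36 kindergartens in 18 pairs".

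Both sections therefore give 150 per arm (300 in total) as the number to be kept, 20% as the loss allowed for, and 180 per arm (360 in total, 18 preschools per arm) as the number to recruit.

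**The concern.** Attrition is a loss among children who have been enrolled, so the number to recruit is the required number divided by the proportion expected to stay. The plan appears to have added 20% to the required number instead. A mark-up of 20% does not cover a loss of 20%, because the loss applies to the larger, marked-up number.

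What is at stake is whether the recruitment target delivers the margin claimed for it. Retention will be judged against 300. At the rate the plan says it has allowed for, 360 recruits do not leave 300.

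**Working it through.** **Inputs, all from the Protocol article.** Required per arm: 150. Attrition allowance: 20%. Recruited: 180 per arm, 360 in total. Number to retain: at least 300. Preschools per arm: 15 before the allowance and 18 after, at about 10 children each. Formative attrition: 11%. Proportions for the vegetable outcome used to size the trial: 63% and 43%, at the 0.05 level.

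**Step 1: reproduce the plan's figures.** Using n × (1 + d) with d = 0.20:
- 150 × 1.2 = 180 per arm, and 300 × 1.2 = 360
- 15 × 1.2 = 18 preschools per arm

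All three match exactly, so this is how the allowance was applied.

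**Step 2: apply the stated loss.**
- 180 × 0.8 = 144 per arm, 6 below 150
- 360 × 0.8 = 288 in total, 12 below 300 (12/300 = 4%)

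**Step 3: find the loss that 360 does cover.**
- 1 − 150/180 = 16.7%
- At 11%: 360 × 0.89 = 320.4, about 320, so the target is met

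**Step 4: the number that would cover 20%.** Using n / (1 − d):
- 150 / 0.8 = 187.5, so 188 per arm (376 in total)
- At 10 per preschool this is 19 preschools per arm: 38 in all, 380 children, and 380 × 0.8 = 304 retained

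**Step 5: effect on power.** The documents give no intracluster correlation (ICC), so a range is assumed. For k preschools of m children per arm, the design effect is 1 + (m − 1) × ICC. The standard error of the difference is √[(0.63 × 0.37 + 0.43 × 0.57) × design effect / (k × m)]. The test is a two-sided t-test at 0.05 with 2(k − 1) degrees of freedom (the documents do not state sidedness), and matching is ignored.

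Worked example at ICC 0.05, where the variance term is 0.2331 + 0.2451 = 0.4782:
- 18 preschools of 8: design effect 1.35; SE = √(0.4782 × 1.35 / 144) = 0.0670; 0.20/0.0670 = 2.99 on 34 df; power 83%
- 15 preschools of 10: design effect 1.45; SE = √(0.4782 × 1.45 / 150) = 0.0680; 0.20/0.0680 = 2.94 on 28 df; power 81%

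Power for three layouts:

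| Assumed ICC | 15 × 10 per arm (the stated requirement) | 18 × 8 per arm (20% loss spread over preschools) | 14.4 × 10 per arm (20% loss as whole preschools) |
|---|---|---|---|
| 0 | 93% | 92% | 92% |
| 0.03 | 86% | 87% | 84% |
| 0.05 | 81% | 83% | 79% |
| 0.10 | 70% | 73% | 68% |

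The 14.4 is 18 × 0.8, a notional average number of preschools remaining. When losses are spread, the six extra preschools (36 rather than 30) offset the smaller head count. When whole preschools go, power is 1 to 2 points below that of the stated requirement.

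**The case against.** The strongest case on the other side is that this changes nothing of substance. The shortfall is 4% and appears only above 16.7% attrition. The formative work points to 11%, at which about 320 children remain. The Recruitment strategy section speaks of likely numbers, not exact ones. The number to recruit can stay at 360. All of this stands, and it is why the point is minor.

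It could also be said that 20% was meant as a mark-up on 150. The text does not bear that reading. It calls the 20% an allowance for attrition, the Recruitment strategy section says up to 20% beside an 11% attrition rate, and 300 is given as a number to retain.

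Nor does the planned multiple imputation rescue the figure. The Analyses section also runs the primary analyses on observed data, and imputation does not raise the number of children retained.

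In the opposite direction, a reader might infer that the trial is underpowered at 20% attrition, or that more children must be enrolled. The documents support neither. With losses spread over preschools, power is within a point of the stated requirement or above it. It drops below 80% in some rows of the table, but at ICC 0.10 the stated requirement of 150 per arm does so too. That comes from the assumed ICC and not from the attrition step. At ICC 0.05 with whole preschools lost, the attrition step does take power just under 80%, to 79%, but this rests on both assumptions together.

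**Conclusion.** The point holds as a minor internal error in a stated sample-size figure. Needing 150 per arm, allowing for 20% attrition and recruiting 180 per arm cannot all be true, and no other part of the article reconciles them. The shortfall at 20% loss is 6 per arm and 12 in total. What is wrong is the 20% attached to 360, not necessarily 360 itself.

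The head-count arithmetic rests only on the plan's own numbers. The statement that power is little affected rests on the assumed ICC range, on a two-sided t-test and on how losses fall across preschools.

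The check takes 150 as the plan's stated requirement and does not validate it. By the same token, 188 per arm is simply 150/0.8 and not an independently justified sample size.

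**What to change.** Keep 360 and correct the Recruitment strategy and Power, sample size and retention sections together. Suggested wording: *Recruiting 360 children (180 per arm, 36 preschools) retains 300 if attrition does not exceed 16.7%. At 20% attrition about 288 (144 per arm, about 8 per preschool if losses are spread evenly) would remain. At the 11% indicated by formative work about 320 would remain.*

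This costs one or two sentences in each section and a slightly less favourable stated allowance. Nobody extra need be enrolled.

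If the sponsor prefers to keep the 20% claim, the target becomes 188 per arm. At 10 per preschool that means 19 pairs (38 of the 68 available preschools, 380 children), which is two more preschools and 20 more children than now planned. If power at 288 is also quoted, the ICC assumed for it should be stated.

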### Analyses

Baseline quantitative data (collected from parents) will be secured prior to treatment allocation, missing values will be scrutinized to check for non-random distribution and primary analyses will be executed twice: once using observed data, and once using multiple imputations under multivariate normal assumptions using methods given by [34], so that all participants will be analysed in their allocated condition. Analyses of variance (with corrections for potential clustering effects of individuals within childcare centres, [32]) will test the between group differences in the primary outcome measure (children’s knowledge about healthy eating, active play and the sustainability consequences of their food and toy selections; interview data will be quantified, after each child’s interview has been transcribed, for the analyses) and the secondary outcome measures (child eating and activity habits) at each assessment time point and across time points for the children. The teachers’ qualitative interviews 6 months post intervention will be analysed using elements of phenomenology and thematic content analysis [35-37]. A process evaluation will be undertaken to identify the key elements of the curriculum interventions that result in significant and positive shifts in children’s knowledge about healthy eating, active play and the sustainability consequences of their food and toy selections.

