## Methods/Design

### Overall study design

This study is a cluster-randomised trial with pre-school classes of 4 to 5 year-old children randomly allocated to either an intervention or control group and will be conducted and reported in line with CONSORT recommendations. Baseline assessment of study variables will occur prior to implementation of the intervention. Follow up assessments will take place immediately following and 6 months post completion of the intervention strategy. The intervention group children will receive the curriculum interventions that their educators develop. The wait-list control group children will receive ‘usual care’, that is, their educator’s usual teaching approaches. The project has been approved by the Victorian Department of Education and Early Childhood Development and has received ethics approval from the Deakin University, Australian Catholic University and Southern Cross University Human Research Ethics Committee (DHREC 2013–220, 2014 39 V, and ECN-14-001, respectively).

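### Preschools are randomised in matched pairs, but the stated analysis has no pair term; if the matching works, its tests are conservative and lose power

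*Protocol article*

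**What the plan says.** The Recruitment strategy section sets out a pair-matched cluster design: "With a likely quota of 10 participants per preschool, 30 preschools (15 matched pairs) are required, 15 randomized to each arm of the study". After the allowance for attrition the count becomes "a total of 36 kindergartens in 18 pairs".

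The Analyses section names the method for the primary and secondary outcomes, analyses of variance "with corrections for potential clustering effects of individuals within childcare centres". Between-group differences are to be tested at each assessment and across assessments. The primary analyses are run on observed data and again after multiple imputation under a multivariate normal model. Clustering within centres is the only dependence mentioned.

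The Overall study design section describes "pre-school classes of 4 to 5 year-old children randomly allocated to either an intervention or control group" and does not mention pairs. The article gives no matching variables, no within-pair correlation and no ICC, and its power section does not refer to pairing.

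**The concern.** When one preschool of each pair goes to each arm, whatever the two share cancels from the treatment difference. A model with a cluster correction but no pair term estimates its error from all the variation between preschools, including the shared part. The estimated standard error then exceeds the true one. Tests reject too seldom under the null, intervals are too wide, and power falls. The trial would accept the constraint of matching without its benefit, for both primary and secondary outcomes.

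A lesser wording problem sits beside this. The unit is called a class in the design section, a preschool or kindergarten in the recruitment section and a childcare centre in the analysis section. If a centre contributed more than one class, these would be different units, and the reader could not tell whether the correction is made at the randomised one.

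**Working it through.** **The plan's own figures.** 300 children / 10 per preschool = 30 preschools = 15 pairs, and 360 / 10 = 36 preschools = 18 pairs, as stated. The plan gives no figure for the effect of matching, so that part rests on assumptions.

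**Inputs.** From the article: k = 15 or 18 pairs, 10 children recruited per preschool, 20% attrition (360 × 0.8 / 36 = 8 retained), alpha 0.05 (taken as two-sided). Assumed: ICC, the share s of between-preschool variance common to a pair, and an effect of d = 0.35 SD.

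**Formulas**, with the outcome scaled to SD 1:
- variance of a preschool mean: v = ICC + (1 − ICC)/m
- correlation of preschool means within a pair: r = s × ICC / v
- true SE of the treatment difference: √(2v(1 − r)/k), which the paired analysis estimates on k − 1 df
- SE estimated without the pairs: about √(2v/k), on 2k − 2 df
- SE inflation: 1/√(1 − r)

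**Numbers, k = 18, m = 8, s = 0.5.**
- ICC 0.06: v = 0.06 + 0.94/8 = 0.1775; r = 0.03/0.1775 = 0.169; SE 0.128 (paired) against 0.140 (unpaired), ratio 1.10.
- ICC 0.15: v = 0.15 + 0.85/8 = 0.25625; r = 0.075/0.25625 = 0.293; SE 0.142 against 0.169, ratio 1.19.

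Power of t-tests on preschool means at one time point (paired: noncentral t; unpaired: 200,000 simulated trials per cell):

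| ICC | s | Power, paired | Power, unpaired | Type I error, unpaired |
|---|---|---|---|---|
| 0.06 | 0 | 65% | 68% | 5.0% |
| 0.06 | 0.2 | 68% | 68% | 4.3% |
| 0.06 | 0.5 | 73% | 69% | 3.2% |
| 0.15 | 0 | 50% | 52% | 5.0% |
| 0.15 | 0.2 | 55% | 52% | 3.7% |
| 0.15 | 0.5 | 64% | 53% | 2.1% |

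With 15 pairs of 10 children and s = 0.5, power is 72% against 67% at ICC 0.06, and 61% against 48% at ICC 0.15.

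**The plan's own effect.** For the vegetable outcome (63% to 43%, so 20 points), with 15 pairs of 10 and ICC 0.05, paired against unpaired power is 76% against 80% at s = 0, 79% against 80% at 0.2, 84% against 82% at 0.5, and 88% against 83% at 0.8. At ICC 0.10 and s = 0.8 it is 87% against 73%.

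**Break-even.** Pairing trades a smaller variance for fewer degrees of freedom. On interval width the two are equal at r = 1 − (t₂ₖ₋₂/tₖ₋₁)². For k = 15 this is 1 − (2.048/2.145)² = 0.088; for k = 18 it is 1 − (2.032/2.110)² = 0.072.

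**Across-time contrasts.** Change from baseline removes the stable part of what pairs share. Assume baseline-to-follow-up correlations of 0.8 for preschools and 0.5 for children. With k = 18, m = 8 and d = 0.35, paired against unpaired power is then 78% against 78% (ICC 0.06, s = 0.5), 76% against 78% (ICC 0.06, s = 0.2), and 76% against 72% (ICC 0.15, s = 0.5).

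**The case against.** The strongest reply is that the absence of a pair term is inferred from silence. The Analyses section is one paragraph of an article, it lists no model terms, and a fuller plan might include the pairs. That stands as a limit on confidence. It does not remove the point: the article states the matching twice, then names the method and the one dependence to be corrected, and the two do not agree.

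Second, a reader might infer that power is certainly lost. The documents do not support this. The loss depends on a within-pair correlation that they do not give. With 15 to 18 pairs, an unpaired analysis is as good or slightly better when matching is weak, and deliberately breaking the match can be defended. That choice should, however, be fixed in advance.

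Third, single-time-point figures describe only part of the plan. At ICC 0.06 the loss all but disappears for change from baseline; at ICC 0.15 with half the variance shared it falls from about 11 points to about 4. This stands, but the article also plans tests at each time point, where the larger figures apply.

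Fourth, a reader might infer that the trial's positive findings would be unsafe. They would not be on this account, since the error is in the conservative direction. Nor does the varied naming of the unit show that the correction is at the wrong level: about 10 children per preschool is compatible with one class each.

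**Conclusion.** The concern holds in conditional form. The randomisation is pair-matched and the stated analysis is not. If the matching is effective, single-time-point tests are conservative (type I error about 2% to 3% in the two cases with half the variance shared) and lose about 4 points of power at ICC 0.06 and about 11 at ICC 0.15. These sizes rest on an assumed 0.35 SD effect, 18 pairs and 8 children per preschool. The loss is smaller for across-time contrasts, and nil or reversed by 2 to 3 points when matching explains little. This is a matter of efficiency and of matching the analysis to the design; it does not raise the false-positive rate. The naming of the unit is a secondary wording point.

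**What to change.** In the Analyses section, pre-specify a mixed model with matched pair as a stratum and a random effect for the randomised preschool, with degrees of freedom based on preschools or pairs. A random pair effect keeps a preschool whose partner drops out. Carry the same pair and preschool structure into the multiple imputation. Use one name for the randomised unit throughout, so that the cluster correction plainly sits at that unit.

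The change is to analysis wording only; recruitment and conduct are unaffected. The costs are about 2 to 3 points of power for a strictly paired test if matching proves uninformative (17 error degrees of freedom instead of 34 with 18 pairs). A strictly paired analysis of preschool means would also lose the whole pair when one preschool withdraws, which is a reason to prefer the mixed model.

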### Measures

At recruitment, parents will be asked to complete an informed consent form confirming their participation in the study. The following measures will be administered at baseline, the end of the intervention and 6 months post intervention.

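### Outcomes are measured at baseline, but the planned ANOVAs name no baseline covariate, which gives up precision and protection against chance imbalance

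*Protocol article*

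**What the plan says.** The Measures section of the protocol article sets one schedule for the outcomes: "The following measures will be administered at baseline, the end of the intervention and 6 months post intervention". Anthropometry says the same of height and weight. Overall study design confirms that a baseline exists: "Baseline assessment of study variables will occur prior to implementation of the intervention".

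The Analyses section names the method: "Analyses of variance (with corrections for potential clustering effects of individuals within childcare centres, [32]) will test the between group differences". It applies this to the primary outcome (the quantified child interview) and to the secondary eating and activity measures, "at each assessment time point and across time points for the children". No section mentions a baseline covariate or an analysis of covariance. The same section runs the primary analyses twice, on observed data and with multiple imputation.

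Three further facts matter. Recruitment strategy describes matched pairs of preschools, 15 per arm with about 10 children each, raised to 18 per arm for attrition. Hypotheses are worded as proportions of children who improve, and the sample size is built on a binary vegetable outcome. BMI z-score has its own slope analysis, which is outside this point.

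**The concern.** The plan collects the best available predictor of each child's follow-up score, the same measure at baseline, and the stated tests do not use it as a covariate.

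- An ANOVA at one follow-up ignores baseline altogether.
- An ANOVA across time points treats baseline as another outcome. With one follow-up, its group-by-time test is a change-score test.
- Read literally, testing at each assessment also includes a between-group test at baseline, which answers no question after randomisation.

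At stake are precision and protection of the estimate in the particular trial that is run. Few units are randomised, so the arms can differ in starting knowledge by chance.

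**Working it through.** **Inputs.** The plan gives no figure for this point: no baseline-to-follow-up correlation r and no intraclass correlation (ICC). Both are assumed below and shown as ranges. The plan's 150 per group is used only as a head count, 15 preschools × 10 children. (A plain two-sided two-proportion calculation for 63% against 43% gives 97, so 150 is not reproduced, but the variance comparison does not depend on it.)

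**Step 1: one follow-up, child level.** With equal variances at both occasions, the variance of the arm difference relative to follow-up-only ANOVA is:

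- follow-up only: 1
- change score: 2(1 − r)
- baseline-adjusted: 1 − r²
- adjusted relative to change: (1 − r²) / [2(1 − r)] = (1 + r)/2

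| r (assumed) | change | adjusted | adjusted ÷ change | cut against follow-up only | cut against change |
|---|---|---|---|---|---|
| 0.3 | 1.40 | 0.91 | 0.65 | 9% | 35% |
| 0.4 | 1.20 | 0.84 | 0.70 | 16% | 30% |
| 0.5 | 1.00 | 0.75 | 0.75 | 25% | 25% |
| 0.6 | 0.80 | 0.64 | 0.80 | 36% | 20% |

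At an effect for which follow-up-only ANOVA has 80% power, adjustment has 83.6%, 89.9% and 93.8% at r = 0.3, 0.5 and 0.6. Change scores have 65.8%, 80.0% and 87.9%.

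**Step 2: two follow-ups averaged.** If one r applies between all three occasions, the variances are (1 + r)/2 for the follow-up mean, (1 + r)/2 + 1 − 2r for its change from baseline, and (1 + r)/2 − r² after adjustment.

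- r = 0.3: 0.65, 1.05 and 0.56
- r = 0.5: 0.75, 0.75 and 0.50

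Adjustment is again the smallest, so the ordering does not come from using one follow-up. The group-by-time test over three occasions has two degrees of freedom and is not identical to this contrast.

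**Step 3: chance imbalance.** Ignoring the matching, the standard error of the baseline difference in SD units is √(2 × DE / n), with design effect DE = 1 + 9 × ICC.

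- n = 150 per arm, ICC 0.05: √(2 × 1.45 / 150) = 0.139. ICC 0.10: √(2 × 1.90 / 150) = 0.159. A difference beyond 0.2 SD then has probability of about 15% and 21% (0.2/0.139 = 1.44; 0.2/0.159 = 1.26).
- n = 180 per arm: 0.127 and 0.145, or about 12% and 17%.

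Matching would lower these figures by an unknown amount.

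**Step 4: what an imbalance D does.** Given D, the follow-up-only estimate shifts by about rD, the change estimate by about −(1 − r)D, and the adjusted estimate by about 0. At r = 0.5 and D = 0.2 SD, the shifts are +0.10, −0.10 and 0 SD. For scale, a medium effect, the size the plan says it can detect, is taken here as 0.5 SD.

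**The case against.** The strongest reply is that a condensed article has been silent, not that it has ruled anything out. A reader might infer that baseline adjustment is excluded; the text does not say so, and a fuller plan may add covariates. That limits how firmly the point can be put. It does not remove it, because the article does name a method, and that method as worded is not the best use of the data.

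Other stronger readings also fail.

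- **That the planned tests are biased or invalid.** Randomisation keeps both ANOVAs unbiased on average, and the across-time analysis does use baseline as a response.
- **That imbalance is likely and passes in full into the effect.** Step 3 supports only that it is plausible; the pairs were matched; and a follow-up-only estimate takes up about rD, not D.
- **That adjustment is worth a fixed number of extra children.** The formulas are child-level with an assumed r, while preschools are randomised. The formulas also assume continuous outcomes and do not carry over to a binary one such as at most one serve of vegetables.
- **That children missing a visit are lost.** This could apply to the observed-data run, but the multiple-imputation run already covers it.
- **That child interviews take place after allocation.** The Analyses section says "Baseline quantitative data (collected from parents) will be secured prior to treatment allocation" and is silent on when interviews occur relative to allocation. Silence does not establish a late interview, and that timing is a separate question outside this point.

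**Conclusion.** The point holds as a matter of efficiency and conditional protection, not of validity. As worded, the time-point ANOVAs ignore baseline and the across-time ANOVA uses it only as a response. Both are generally less precise than baseline adjustment, and neither removes the effect of a chance imbalance that is plausible with 15 to 18 preschools per arm.

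The size is illustrative: a variance cut of 16% to 36% against follow-up-only ANOVA and of 30% to 20% against change scores for assumed r = 0.4 to 0.6, falling to 9% against follow-up-only at r = 0.3. It rests on child-level formulas, one follow-up, equal variances and a continuous score. The real gain depends on preschool-level and within-preschool correlations that the documents do not give. The baseline significance test is a minor matter: it biases no follow-up estimate, but it serves no purpose.

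**What to change.** Replace the ANOVAs with a clustered mixed model of the two post-baseline assessments: linear for continuous scores, logistic for binary outcomes. Include arm, time, arm × time, the child's own baseline value of the same outcome, matched pair, and random effects for preschool and child. The arm × time terms still give the comparison at each follow-up. Fit the same model in the observed-data and the multiple-imputation runs. Drop the between-group significance test at baseline and report baseline values descriptively.

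The cost is a change to the analysis wording. No new data or visits are needed. A child without a baseline value would leave the observed-data model, and the multiple-imputation run covers that case.
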